### Primary outcome measure

The severity of UI at 24 months is the primary outcome, as measured by the validated ICIQ-UI SF which encompasses urinary leakage frequency, amount and interference with everyday life (total score 0–21, higher score indicates more severe UI).^21^

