### Randomisation

Women who are eligible and willing to take part will be randomised to either the experimental or control group via the automated computer randomisation application developed at the CHaRT, University of Aberdeen. The web-based application will be accessed by staff at the centre to determine the participant’s group. Allocation will be minimised on: type of UI (stress UI or mixed UI), centre, age (<50/≥50 years) and UI severity at baseline (ICIQ-UI SF score <13/≥13).^30^

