### Statistical analysis and sample size

All analyses will be according to the Statistical Analysis Plan and Health Economic Analysis Plan that will be agreed in advance with the Project Management Group (PMG) and the Trial Steering Committee (TSC). A single main analysis will be performed at the end of the trial when 24-month follow-up has been completed. An independent data monitoring and ethics committee (DMEC) will review confidential interim analyses of accumulating data at its discretion, at least annually. Analysis will be based on the intention-to-treat principle, such that women will be analysed in the groups to which they were allocated regardless of the intervention received.

The main effectiveness analysis will estimate the mean difference in the primary outcome (ICIQ-UI SF score) (and 95% CIs) between the experimental and control groups at 24 months using a general linear mixed model, adjusting for minimisation covariates, therapist type and baseline score. Centre and therapist type will be fitted, where possible, as random effects. Missing outcome data will be estimated using multiple imputation and included in a sensitivity analysis Secondary outcomes will be analysed in a similar manner using an appropriate generalised linear model. Complier average causal effect analysis of the primary outcome will be conducted to investigate the impact of non-compliance. Subgroup analyses by type of incontinence (stress UI or mixed UI), type of therapist (physiotherapist or nurse), participant age (<50/≥50 years) and baseline UI severity (ICIQ-UI SF score <13/≥13) are also planned.

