The primary economic outcome measure of cost effectiveness is incremental cost per QALY at 24 months undertaken from the NHS perspective. QALYs will be based on responses to the EQ-5D-3L^30^ and the ICIQ-LUTSqol.^24^ Personal patient resource use data will be incorporated into the analysis to report on a wider perspective. Where appropriate the analysis of incremental costs, effectiveness and cost-effectiveness will be based on similar statistical models as those outlined in the statistical analysis section above. This ’within' trial analysis will include both deterministic and stochastic sensitivity analyses to explore statistical and other forms (eg, around unit costs or the source of utility estimates) of uncertainty. Similar subgroup analysis will be performed in the economic analysis as defined in the statistical analysis if deemed relevant. If relevant an economic model will be developed to provide additional information for policy-makers.

Assuming a clinically meaningful difference of 3 points on the ICIQ-UI SF score (eg, change from leaking urine ‘once a day’ to ‘never’), which is similar to the minimal clinically important difference of 2.5 reported in a study of older women,^31^ and a conservative estimate for the SD of 10, a sample size of 234 per group would detect this difference (standardised effect size of 0.3) with 90% power at the 5% level of significance (two-sided alpha). Allowing for 22% drop out, we will randomise 300 women per group. With 600 subjects, we will also have 90% power to detect important differences in secondary outcomes.

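### The stated subgroup analyses split age and baseline severity at the minimisation cut-offs; prespecified continuous interaction terms would use the same data with more power if effect modification is roughly linear

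*Protocol article*

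**What the plan says.** Under Statistical analysis and sample size, the Protocol article lists four subgroup factors. Type of incontinence and type of therapist are categorical by nature. The other two are numeric variables given with one cut-off each: "participant age (<50/≥50 years) and baseline UI severity (ICIQ-UI SF score <13/≥13) are also planned".

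The Randomisation section uses the same groupings as minimisation factors: "age (<50/≥50 years) and UI severity at baseline (ICIQ-UI SF score <13/≥13". The cut-offs are therefore prespecified, but they come from the allocation scheme, and no reason is given for expecting the treatment effect to change at 13 points or at 50 years.

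The Primary outcome measure section describes the severity measure as a numeric scale ("total score 0–21, higher score indicates more severe UI"). The main model is described as "adjusting for minimisation covariates, therapist type and baseline score", so the baseline score is already used as a covariate in its own right.

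Analysis detail is referred to another document that is not shown: "All analyses will be according to the Statistical Analysis Plan and Health Economic Analysis Plan". The article claims no power for any subgroup or interaction.

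**The concern.** Minimisation needs categories; a test of effect modification does not. A two-group split treats women scoring 12 and 13 as different and women scoring 13 and 21 as alike. If the benefit of biofeedback rises or falls steadily with severity or age, this discards part of the information on that gradient, and a real one is more likely to be missed.

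Whether biofeedback works differently in more severe or older women is a question the trial has chosen to ask. Interaction tests are weak in a trial sized for a main effect, so the form of the test matters. What is at stake is the sensitivity of two secondary analyses. The validity of the tests is not in doubt: both forms hold the type I error at about 5%.

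**Working it through.** **The plan's own figure.** Inputs from Statistical analysis and sample size: difference 3 points, SD 10, two-sided alpha 0.05, power 90%, dropout 22%.

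- n per group = 2 × (1.960 + 1.282)² × 10² / 3² = 233.5, rounded up to 234.
- 234 / (1 − 0.22) = 300 per group.

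Both figures reproduce. The analysed total is 2 × 234 = 468.

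**Assumptions not in the documents.** The modifier is roughly normal; the treatment effect changes linearly with it; a share p of women lies above the cut-off (range 0.5 to 0.2, since the article does not say where 13 points or 50 years falls in the population). The 3-point difference in effect between subgroups is borrowed from the main-effect target for illustration. Two SDs are shown: the planning value of 10 and an assumed 5. An SD of 10 is close to the largest possible on a 0 to 21 scale (21 / 2 = 10.5), and the article itself calls it conservative ("a conservative estimate for the SD of 10").

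**Information kept by the split.** With c the standard normal cut-point and φ the normal density, the efficiency of the split relative to the linear term is φ(c)² / [p(1 − p)].

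- p = 0.5: 0.3989² / 0.25 = 0.64, so 468 women act like about 298.
- p = 0.4: 0.62, about 291.
- p = 0.3: 0.58, about 269.
- p = 0.2: 0.2800² / 0.16 = 0.49, about 229.

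**Power with the split.** SE of the interaction = SD × √[4/(np) + 4/(n(1 − p))], with n = 468.

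- SD 10, p = 0.5: SE = 1.849; 3 / 1.849 = 1.62; power = Φ(1.62 − 1.96) = 37%.
- SD 10, p = 0.2: SE = 2.311; 3 / 2.311 = 1.30; power = 25%.

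**Power with the continuous term.** Take the slope per SD of the modifier that gives the same 3-point difference between the two group means. The gap between those means is φ(c)/p + φ(c)/(1 − p), in SD units of the modifier. The SE of the slope is 2 × SD / √n.

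- SD 10, p = 0.5: gap 1.596; slope 3 / 1.596 = 1.880; SE = 20 / 21.63 = 0.9245; z = 2.03; power = 53%.
- SD 10, p = 0.2: gap 1.750; slope 1.714; z = 1.85; power = 46%.

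The same steps give:

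| SD | p | Split | Continuous |
|---|---|---|---|
| 10 | 0.5 | 37% | 53% |
| 10 | 0.4 | 36% | 52% |
| 10 | 0.3 | 32% | 50% |
| 10 | 0.2 | 25% | 46% |
| 5 | 0.5 | 90% | 98% |
| 5 | 0.4 | 89% | 98% |
| 5 | 0.3 | 85% | 98% |
| 5 | 0.2 | 74% | 96% |

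**A second scenario.** Assume a baseline SD of 4, an effect that changes by 0.25 points per baseline point, and a median split.

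- Residual SD 4.3: z = 0.25 × 4 × √468 / (2 × 4.3) = 2.52, power about 71% continuous. Multiplying z by √0.64 gives 2.01, about 52% with the split.
- Residual SD 10: z = 1.08, about 19%, against 0.86, about 14%.

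The direction is the same throughout; the size of the gain depends heavily on the residual SD.

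**The case against.** The strongest reply is that this is a preference and not an error. The cut-offs are prespecified and match the minimisation factors, so they are not data-driven; two-group estimates are conventional and easy to read; and the article claims no subgroup power. All of that stands, and it is why the two-group estimates should be kept for presentation.

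A second reply is that the functional form of an interaction belongs in the SAP. This stands in part. A reader might infer that effect modification will be examined only through the cut-offs. The article does not say so: it lists planned subgroups, and the SAP, which is not shown, may add a continuous interaction. What remains is that the article does state a form for these two analyses. The point concerns that stated form, not missing detail.

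Third, the loss is conditional. With a true step at 13 points or 50 years, the split would be the more efficient test. The documents give no reason to expect a step there, and none to rule it out.

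Fourth, the continuous term does not rescue power. At SD 10 both tests fall far short of 90% for a 3-point interaction. This is correct; the gain is relative, and decides adequacy only if the residual SD is well below 10.

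A reader might also infer that the primary model shares the weakness, because it adjusts for minimisation covariates. The documents do not support this. The baseline score is named as a separate covariate, so a <13/≥13 term beside it costs about one degree of freedom and does not bias the treatment effect. The article does not state how age is coded in the model, and adjusting for the factors as used in allocation is defensible.

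**Conclusion.** The point holds as a minor improvement to two secondary analyses. The stated plan examines effect modification by age and baseline severity through the minimisation cut-offs and mentions no continuous interaction, although a 0 to 21 baseline score is collected.

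Under a roughly linear gradient in a roughly normal modifier, the split gives up about 36% of the information at a median cut and about 51% at an 80/20 cut. In the 3-point illustration this is 16 to 20 percentage points of power at SD 10, and about 8 to 22 at an assumed SD of 5. Linearity, normality, the share above each cut-off and the SD of 5 are assumptions. So is the availability of age in years, which the article does not state but which the eligibility criterion and the 50-year split imply.

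The conclusion does not extend to the primary analysis. The primary model and the sample size of 234 analysed and 300 randomised per group need no change on this ground.

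**What to change.** Before the 24-month analysis, specify in the SAP that effect modification by baseline severity and by age will be tested with treatment-by-baseline-score and treatment-by-age interactions on the continuous variables. Use a linear term for each, with a spline check of its form. Keep the <13/≥13 and <50/≥50 estimates, with confidence intervals, for presentation. If the SAP already does this, nothing more is needed.

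The timing matters: the cut-offs are published, so a later move to continuous terms could look data-driven.

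The cost is SAP wording, with no new data collection provided age is held in years. The one downside is a functional-form assumption, which the spline check addresses.

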### Safety measures

The OPAL trial involves treatments for UI which are well established in clinical practice, therefore adverse effects (although these are unlikely) will be those observed in everyday practice associated with the use of PFMT and biofeedback. In the OPAL trial, all serious adverse events experienced by a research participant will be reported to the main research ethics committee if they occur within 30 days of the participant’s last PFMT appointment and where in the opinion of the Chief Investigator and/or the Chair of the DMEC the event is related and unexpected.

### Patient involvement

Women with experience of UI are involved in the design, delivery and oversight of the trial through membership on the PMG and TSC. A lay summary of the findings will be sent to participants involved in the trial.

## Ethics and dissemination

The trial will be conducted in accordance with the International Conference on Harmonisation Good Clinical Practice (ICH GCP)) Note for Guidance on Good Clinical Practice. Trial safety and progress will be overseen by the independent DMEC and the TSC. Meetings of these committees will take place annually.

Final trial results will be disseminated to the funding body, the NIHR Health Technology Assessment Programme. The trial results will then be submitted to peer-reviewed international academic journals and presented at international conferences. Results will also contribute to the relevant Cochrane review. Participants will be provided with a summary of the results.
